#### Cardiorespiratory fitness

Submaximal heart rate, blood pressure, blood oxygen saturation (SpO_2_, Vacumed, Venura CA), rating of perceived exertion (Borg CR10 scale) 
[31], ventilatory threshold (VT) and peak oxygen uptake (VO_2_ peak) will be determined during a modified Bruce 
[32] graded exercise test on a treadmill. The modified Bruce treadmill protocol will be used because of the nature of the participants (e.g., large age range, varied fitness levels). During each treadmill test, all expired air will be collected and analyzed with a calibrated TrueOne metabolic measurement system (ParVo Medics Inc, Sandy, UT.). VT will be determined using the V-slope method of Wasserman 
[33] and VO_2_ peak will be determined as the highest oxygen uptake achieved during the treadmill test to volitional exhaustion. Recovery heart rate and systolic blood pressure will be measured 1 and 5 minutes after the treadmill test ends.

*Muscular strength* will be assessed using multiple repetition maximum (mRM) strength tests for chest press and leg press to determine the maximum weight an individual can lift approximately 8 – 10 times. The protocol will follow the National Strength and Conditioning Association guidelines 
[34]. The mRM will be used to predict a 1RM using the formulae reported by Mayhew et al. 
[35]. Combined grip strength (kg) of the right and left hands will be measured using a JAMAR hydraulic hand dynamometer (Lafayette Instruments, ID). A sum will also be calculated from the best score of 2 trials recorded for each hand according to the CPAFLA protocol 
[30].

*Muscular Endurance* of the abdominals will be assessed by a partial curl-up test and will be performed according to a standardized protocol 
[30,36]. Upper body muscular endurance will be assessed using the chest press exercise device described previously at a relative load of 50% of predicted 1RM. Lower body muscular endurance will be done using leg press at 70% of predicted 1RM.

*Flexibility* will be assessed by a trunk forward flexion sit-and-reach test using a Wells-Dillon flexometer according to a standardized protocol 
[30].

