[43]. We selected recurrence-free interval (RFI) as our primary disease endpoint because it consists of events directly attributed to breast cancer including invasive ipsilateral breast tumor recurrence, local/regional invasive recurrence, distant recurrence, and death from breast cancer. We will also examine other composite disease endpoints as secondary endpoints including overall survival, invasive disease-free survival, distant disease-free survival, distant relapse-free survival, breast cancer-free interval, and distant recurrence-free interval. Finally, we will examine the single disease endpoints of death from breast cancer and death from non-breast cancer. These endpoints will be abstracted by the health records technicians at the time of the medical chart reviews described above.

Information on all deaths that occurred in the province is provided by Vital Statistics Alberta (VSA) to the ACR on a monthly basis with underlying cause of death provided by Statistics Canada to VSA. There is an average three-month time lag between the actual death occurrence and reporting to the ACR. For cases that leave the province after diagnosis, several mechanisms exist to capture their deaths with reciprocal agreements between other provinces and record linkages with the Canadian Mortality Database that are undertaken with the ACR data. These agreements and processes ensure that vital status can be determined for over 95% of cases. For cases who have left the province and who are not known to be dead, the date of leaving Alberta will be used as the censoring time. For the follow-up of this cohort, yearly checks of the vital status of the breast cancer survivors will be conducted through linkages with the ACR. Cause of death and date of death will be obtained from this source.

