### Sample size and power considerations

Although a cohort study such as this one has many exposures, time points, and endpoints of interest, we chose to power our study using cardiorespiratory fitness at one-year follow-up as the primary exposure/time point, and recurrence free interval (RFI) as the primary endpoint because of the importance of these variables but also because of the substantial power needed to detect this association. By designing the study with adequate power for this association, we ensured sufficient power for all the other objectives that require substantially less power. We designed the study to detect a 30% risk reduction of RFI in survivors who are in the top quartile of cardiorespiratory fitness, compared to those who are in the lowest quartile (hazard ratio = 0.7). The sample size was determined under the framework of Cox proportional hazards (PH) models, adjusting for known potential confounders such as age, BMI, tumor stage, treatment, alcohol intake, diet, smoking and co-morbidity. A statistical power of 80% and a two-sided α = 0.05 were used. This setting requires 223 to 401 events (PASS 2005); the exact number depends on how strong the association is between cardiorespiratory fitness and the confounders in the Cox PH model. A stronger association requires a larger number of events. The association among variables is quantified by *R*^*2*^ of a multiple linear regression model where cardiorespiratory fitness is regressed onto the confounders. In the above calculation, we have considered a range of *R*^*2*^ between 0.1 (requiring 223 events) and 0.5 (requiring 401 events) that we deemed realistic. The *R*^*2*^ can be reduced by using cardiorespiratory fitness quartiles that are adjusted for some of the major confounders such as age and BMI, ensuring the *R*^*2*^ value of less or equal to 0.5. Thus, our study is sufficiently powered for the primary objective if we have more than 401 events.

The annual recurrence rate for localized invasive breast cancer is estimated to be 2 ~ 3% 
[44]. For stage I – IIIc patients combined, a first five-year recurrence rate of 20% has been reported 

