[45,46]. To attain the desired number of events, we are using a stratified sampling design based on the projected breast cancer cases diagnosed in 2012–15 who will be treated in Edmonton or Calgary. We plan to recruit a total of 1500 breast cancer survivors from the two locations. Given the projected numbers of survivors seen at two locations for each stage, and, assuming an overall 50% consent rate for participation, the recruitment will be completed within 5 years. This recruitment plan will provide a median of about seven years of follow-up by the end of this study in year 2022, and will yield a minimum of 460 events. Allowing for a 10% loss to follow-up, we expect to observe, at minimum, 414 events in this cohort.

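### The 414 expected events are counted over the whole cohort, but the 401 required apply only to women with a one-year fitness value, and no separate allowance is made for missing tests

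*Protocol article*

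**What the plan says.** All references are to the protocol article. Under Sample size and power considerations the study is powered "using cardiorespiratory fitness at one-year follow-up as the primary exposure/time point", with recurrence-free interval as the endpoint and a hazard ratio of 0.7 between the top and lowest fitness quartiles. "A statistical power of 80% and a two-sided α = 0.05 were used". The required number of events runs from 223 (R² = 0.1) to 401 (R² = 0.5), where R² comes from regressing fitness on the confounders. The section concludes that "our study is sufficiently powered for the primary objective if we have more than 401 events". It forecasts at least 460 events from 1500 women and then makes one deduction: "Allowing for a 10% loss to follow-up, we expect to observe, at minimum, 414 events in this cohort".

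Under Cardiorespiratory fitness, VO2 peak is "the highest oxygen uptake achieved during the treadmill test to volitional exhaustion". Study design places the clinic measures at baseline, one year and three years. Outcomes are collected by another route. Under Medical record abstraction, registry technicians abstract the charts of all participants, and registry linkage is said to ensure that "vital status can be determined for over 95% of cases".

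**The concern.** Exposure and outcome can be lost separately. A woman who misses the one-year visit, or attends but cannot complete the treadmill test, may still be followed through her chart and the registry. Her recurrence would count among the 414, yet without a fitness value it does not directly inform the quartile comparison for which 401 events are needed. The sufficiency statement therefore sets one population's events against another population's requirement.

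The difference matters because the margin is small at the R² on which the authors base their conclusion. The same section also rests the adequacy of power for all other objectives on this calculation.

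**Working it through.** **Inputs from Sample size and power considerations.** 460 events before loss; 10% loss to follow-up; 401 events required at R² = 0.5 and 223 at R² = 0.1; 80% power; two-sided α = 0.05. The share of women without a valid one-year VO2 peak is not given, so it is varied as an assumption. All 460 events are granted.

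**1. The plan's own figure.** 460 × (1 − 0.10) = 414, which reproduces exactly. Margin: 414 − 401 = 13 events, and 13/414 = 3.1%.

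**2. Consistency of the requirement.** If required events scale as 1/(1 − R²), the base is 401 × 0.5 = 200.5 and 223 × 0.9 = 200.7. The two ends agree, so required events = 200.5/(1 − R²).

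**3. Power at R² = 0.5 with a share m missing.** Events D = 414 × (1 − m), assuming missingness is unrelated to event risk. Calibrated so that 401 events give 80%, power = Φ(2.8016 × √(D/401) − 1.96).

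| m (assumed) | D | Power |
|---|---|---|
| 0% | 414 | 81.2% |
| 3.1% | 401 | 80.0% |
| 5% | 393 | 79.2% |
| 10% | 373 | 77.1% |
| 20% | 331 | 72.1% |

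**4. If the 10% covers both losses.** With an assumed registry loss of 5%, 460 × 0.95 = 437 events are followed. The tolerable share of missing tests is 1 − 401/437 = 8.2%.

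**5. Tolerable missing share at other R².** This is 1 − [200.5/(1 − R²)]/414.

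| R² | Events required | Tolerable missing |
|---|---|---|
| 0.5 | 401.0 | 3.1% |
| 0.45 | 364.5 | 11.9% |
| 0.4 | 334.2 | 19.3% |
| 0.3 | 286.4 | 30.8% |
| 0.1 | 222.8 | 46.2% |

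**6. Largest R² that keeps 80% power.** This is 1 − 200.5/D. With 20% missing, 1 − 200.5/331.2 = 0.39.

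**7. Events versus women.** The 3.1% is a share of events. It is also a share of women only if missingness is unrelated to risk. If untested women had 1.5 times the event risk (an assumption), the share of events lost would be 1.5m/(1.5m + 1 − m). Setting this to 3.14% gives m = 0.0314/(1.5 − 0.5 × 0.0314) = 2.1% of women.

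**The case against.** The strongest reply is that 3.1% is a worst case. R² = 0.5 is the top of the range considered, and the authors propose fitness quartiles adjusted for age and BMI to keep R² at or below it. At R² = 0.4 the plan survives 19% missing. Even at 0.5, 10% missing costs only about three points below 80%, and 460 and 414 are described as minimums. This limits the size of the problem. It does not remove it, because 0.5 is the bound at which the article declares itself sufficiently powered, and no amount by which events might exceed the minimum is given.

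The 10% is also undefined. Since registry linkage covers over 95% of cases for vital status, part of the 10% could be meant for missed visits. That reading is possible, and the 8.2% limit reflects it. The text does not say so, and it describes the 414 as events in the cohort.

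A reader might infer that the least fit or sickest women drop out and that the hazard ratio is biased as a result. The article does not show this. It states neither who will miss the test nor that only complete cases are analysed. Several provisions limit untestability: readiness screening at entry, a modified Bruce protocol chosen for varied fitness levels, and testing that can be split over two visits. Quartiles formed among tested women would be redefined, not emptied at the bottom. Missingness that depends only on fitness and the modelled covariates need not bias a complete-case hazard ratio. Selective loss remains plausible for an exhaustion test a year after enrolment, but as a risk only.

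A reader might also treat the lack of an imputation method as a fault. In a condensed article it is not, since that can sit in the analysis plan.

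**Conclusion.** The point holds for the event count. The subtraction from 460 to 414 is correct, but its result is compared with a requirement for women who have the one-year exposure, with no separate allowance for those who do not. At R² = 0.5 the stated 80% power has a margin of 13 events. It falls below 80% when more than 3.1% lack the test, or 8.2% on the generous reading of the 10%. The shortfall is modest at first (79% and 77% power with 5% and 10% missing) and larger at 20% missing (72%). Over most of the stated R² range the plan tolerates considerably more.

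These figures rest on assumed missing shares, on missingness unrelated to risk, and on 401 taken at face value. The last is a real caveat. A Schoenfeld calculation with the stated two-sided inputs, an even split and R² = 0.5 gives 494 events, so the 3.1% measures distance from the plan's own criterion and is not an independent estimate of the margin. It would be too strong to say that the study loses its power whenever 3.1% of tests are missing, because that omits the R² condition.

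**What to change.** In Sample size and power considerations:

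- State whether the 10% covers loss of outcome follow-up only, or missed one-year testing as well.
- Restate expected events as those among women with a valid one-year VO2 peak, showing the assumed test completion rate.
- Give the power at R² = 0.5 for that count, or the largest R² at which 80% power holds (about 0.39 if 20% are missing).

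Handling of missing tests, for example multiple imputation using baseline fitness and other collected data, can be left to the analysis plan. No extra participants or visits are needed. The cost is a less favourable stated power.

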## Discussion

The primary focus of the AMBER Study will be to identify the independent and interactive associations of PA and HRF with disease outcomes (e.g., recurrence, breast cancer-specific mortality, overall survival). Other important health outcomes will include treatment completion rates, symptoms and side effects (e.g., pain, lymphedema, fatigue, cognitive dysfunction), and PROs (e.g., QoL, anxiety, depression, self-esteem, happiness). We will also be able to examine the mediators and moderators of any observed associations between PA, HRF, and health outcomes. Finally, we will be able to identify the key determinants of PA and HRF including demographic, medical, and social cognitive variables, at various time points across the survivorship trajectory. Taken together, these data will provide a detailed understanding of the unique benefits, risks, and determinants of PA and HRF at multiple time points of survivorship so that intervention strategies can be developed to help breast cancer survivors achieve and maintain healthy levels of PA and HRF. The AMBER Study is designed initially to address the following five major research themes.

### Physical activity, health-related fitness, and disease outcomes

The primary aim of this project is to examine the associations between self-reported and objective PA (including sedentary behavior), HRF (including body composition), and disease outcomes in breast cancer survivors (including recurrence-free interval, breast cancer mortality, and overall survival). These data will provide critical information on the optimal type, volume, and pattern (i.e., how the volume is achieved over a given week) of PA that may be most strongly associated with disease outcomes in breast cancer survivors. Moreover, while previous studies have used self-report PA assessments, the use of accelerometers to measure PA will provide an accurate (and gold-standard) estimate of PA at multiple time points across the survivorship trajectory. Further, no studies have examined associations between objectively-determined PA and disease endpoints. Multivariable analyses will be able to determine any independent associations of the PA and HRF variables with disease outcomes that may identify one or more PA-related exposures of primary importance. For example, two research questions will be to determine whether: (a) cardiorespiratory fitness and muscular strength or other HRF assessments are independently associated with disease outcomes among breast cancer survivors, and (b) vigorous PA and sedentary behavior are independently associated with disease outcomes. A secondary aim is to examine potential moderators (effect modifiers) of the associations between PA, HRF, and disease outcomes. These data will provide critical information on which subgroups of survivors may benefit the most from engaging in PA and may also even identify different optimal PA prescriptions for different survivor subgroups. The ultimate goal of this project is to provide insights regarding the relative importance of various aspects of the PA prescription and the various HRF components for breast cancer outcomes that will be directly relevant for PA and sedentary behavior recommendations for breast cancer survivors.

### Physical activity, health-related fitness, and biologic mechanisms

The primary aim of this project is to examine the mechanisms that may explain any associations between self-reported and objective PA (including sedentary behavior), HRF (including body composition), and disease outcomes in breast cancer survivors (including recurrence-free interval, breast cancer mortality, and overall survival). The exact biologic mechanisms whereby PA and HRF may influence breast cancer recurrence and survival have not yet been delineated. More research has focused on the role of PA in breast cancer incidence. One hypothesized biologic model for postmenopausal breast cancer risk implicates adiposity, sex hormones, insulin resistance and chronic inflammation as mediators of PA 
[47]. This model is further supported by recent results from exercise intervention trials that demonstrated a direct impact of PA on sex hormones 
[48,49] and adiposity levels 
[50], which are both convincingly associated with postmenopausal breast cancer risk in the epidemiologic literature 
[47]. The same model and biologic rationale relating PA to postmenopausal breast cancer risk 
[47] can be adapted to breast cancer recurrence and survival since many of the same biomarkers have been associated with PA in breast cancer survivors, and breast cancer recurrence/survival, respectively. Adaptations to the model include the addition of breast cancer therapies and their potential influence on biomarkers 
[51,52] as well as the addition of insulin-like growth factor 1 (IGF-1) and IGF binding protein 3 (IGFBP-3). HRF (i.e., body composition, muscular strength, muscular endurance, cardiorespiratory fitness) can also be added to the model since body composition is influenced by PA, changes in muscle mass may affect insulin resistance, and in one recent healthy cohort study, cardiorespiratory fitness was found to decrease risk of breast cancer death through an unknown mechanism 
[53].

Clearly, there is a lack of consistent information relating PA and breast cancer outcomes to our hypothesized biomarkers. A better understanding of the underlying biologic pathways involved in the association between PA and breast cancer outcomes could be gained with a sufficiently powered study using more accurate measures of body fat, valid measures of PA, and careful control for patient and tumor-related moderators of the effects of PA on breast cancer outcome. Serial measurements of our proposed biomarkers over time will be a novel attribute of this study and will enable us to identify significant time points for influencing breast cancer outcome and the effect of biomarker level changes over time. This understanding will add biologic plausibility to the association between PA and breast cancer outcome, guide future epidemiologic research, identify new targets for interventions, and inform clinical recommendations for improving survival after breast cancer diagnosis.

### Physical activity, health-related fitness, and patient-reported outcomes

The primary aim of this project is to examine the associations between PA, HRF, and PROs across the breast cancer continuum. Breast cancer survivors have an elevated risk for poor QoL, anxiety, depression, fatigue, and cognitive impairment both during treatment 
[54] and throughout survivorship 
[55,56]. Some evidence suggests that women surviving cancer may continue to demonstrate poor function on various PROs for up to 10 years after their initial diagnosis 
[57-59]. While preventing declines in PROs after a breast cancer diagnosis is important, new research is suggesting that less decline in QoL during adjuvant therapy for breast cancer may also be associated with a reduced risk of breast cancer recurrence 
[60] (Sarenmalm et al., 2009).

Systematic reviews support the role of PA as a safe and effective intervention to improve HRF and selected PROs in breast cancer survivors, particularly during survivorship 
[61,62]. The most commonly studied PROs in PA research are fatigue, QoL, physical functioning, depression, and anxiety 
[62]. Systematic reviews provide evidence that PA can improve patient-reported physical functioning and anxiety during treatment, and QoL, fatigue, depression, and anxiety during survivorship. In particular, these studies suggest that particular QoL domains, especially physical well-being, functional well-being, and fatigue appear to be domains that are most likely affected by PA. Indeed, some data suggest that improvements in several PROs are dependent on changes in HRF such as cardiorespiratory fitness 
[63,64].

Although over 50 randomized controlled trials (RCTs) have examined the effects of PA on PROs in breast cancer survivors 
[62], few of these trials have had adequate power for subgroup analysis, few have examined the optimal *type* of PA (e.g., aerobic, resistance) or *intensity* of PA (e.g., light, moderate, vigorous activities), few have examined the HRF components most relevant to PROs, and few have examined the effects of PA or HRF on PROs across the continuum of breast cancer survivorship (e.g., treatment, early survivorship, later survivorship). Little is known about other relevant PROs such as cognitive function, taxane symptoms, hormonal symptoms, and psychological well-being (e.g., happiness and satisfaction with life). Further, to date there are no studies examining sedentary behavior (time spent sitting) and associations with PROs among breast cancer survivors. Information of this nature may facilitate further understanding of how PA and sedentary behavior is related to PROs during breast cancer survivorship. This project will also examine important mediators and moderators of the associations between PA, HRF, and PROs.

### Physical activity, health-related fitness, and physical functioning

This project will examine the relationship between PA, HRF and the incidence, severity and natural progression of lymphedema and upper limb morbidity (e.g., pain, numbness, weakness and shoulder dysfunction) from diagnosis through treatment and recovery from breast cancer. Lymphedema is a chronic swelling of the limb on the surgical side that may present immediately or many years after treatment 
[65,66]. More recent estimates suggest an incidence rate of around 20%, with higher rates found in studies with longer follow-up 
[67,68]. Lymphedema is a known consequence of surgical and radiotherapeutic techniques and is known to have deleterious effects on QoL 
[69]. Among systemic factors, obesity has been associated with increased lymphedema risk 
[70]. While PA has been traditionally viewed as a possible risk factor, PA has not been associated with lymphedema in prospective research and more recent evidence suggests a possible protective effect of PA 
[71].

Upper limb morbidity occurs frequently following treatment for breast cancer 
[71,72] and recent evidence suggests symptoms such as pain and shoulder dysfunction are more prevalent than lymphedema 
[72]. Although upper limb morbidity is reduced with newer techniques such as Sentinel Lymph Node Biopsy, studies have shown that a majority of breast cancer survivors have at least one upper limb symptom (e.g., numbness, pain, weakness, swelling, stiffness) in the long term 
[67].

Peripheral neuropathy is a condition that results from damage to or dysfunction of the peripheral nerves 
[73]. In breast cancer survivors this damage may occur from administration of a neurotoxic chemotherapeutic agent 
[73]. Sensory symptoms associated with chemotherapy induced peripheral neuropathy include numbness, tingling and pain that presents in the distal aspects of the upper and lower extremities, often described as a stocking/glove distribution 
[74]. Motor symptoms associated with the condition may include upper and lower limb weakness, impaired proprioception and balance. Functional impairments may result in difficulty performing fine motor tasks, walking and increase the risk falling 
[74]. Thus, breast cancer survivors experiencing treatment related effects such as lymphedema, upper limb morbidity and peripheral neuropathy, may have unique challenges that impact their PA, HRF, and PROs.

